**Study Outcome Measures**

The **primary study objective** is to establish whether Halo will decrease the frequency, duration, and severity of acute respiratory disease and decrease the detection of respiratory viruses by multiplex PCR. After enrollment, subjects will be seen at scheduled monthly visits (+/- 7 days), 1-2 months after study completion and at interim visits when they develop a syndrome consistent with an acute upper respiratory disease. An acute upper respiratory disease will be defined as having fever to > 37.8°C and a non-productive cough and 2 or more of the following symptoms:

- Sore throat
- Rhinorrhea
- Sinus congestion
- Malaise

Patients will be provided with diaries (RedCap) to note any illness especially acute respiratory disease and to record the duration of each sign or symptom. Subjects will also be asked to take their temperature at 5p.m. each day and record their temperatures in the diaries. At interim visits related to the development of acute upper respiratory illness oropharyngeal swabs will be obtained for bacterial and fungal culture as well as respiratory virus multiplex PCR.

**Multiplex RT-PCR:** Following collection, an aliquot of the clinical sample will be placed in viral freezing media and stored at -80 degrees. Samples will be placed in 2ml glass collection tubes at a 1:1 ratio of clinical sample to viral freezing media. RNA from each clinical specimen will be extracted with the QiaAmp Viral RNA Mini Kit (Qiagen Inc., Valencia, CA) according to the manufacturer’s protocol. Extracted RNA will be stored at -80 degrees until processing.

Primers and probe sets for multiplex real-time RT-PCR detection of respiratory tract viruses have already been described [[35](#_ENREF_35)]. We will screen influenza positive samples under conditions as described with the exception that chlamydia and mycoplasma primer sets will be omitted. In addition, screening reactions for recently recognized viruses will be performed separately using real time primer sets as previously described [[36](#_ENREF_36), [37](#_ENREF_37)].

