Microbial cultures will be performed from oral swabs obtained from enrolled study participants. Briefly, collected swabs will be vortexed in 1 mL saline, and a calibrated 10 µL inoculation loop will be used to spread the resulting suspension (and its serial dilutions) onto agar plates specific for aerobic or anaerobic bacteria (blood agar), or fungi (Sabouraud dextrose). Plates will be incubated at 37 °C overnight and the resulting CFUs will be counted to determine the microbial load.

In terms of safety and tolerance of Halo and placebo, the oropharynx and gingiva will be examined for erythema and ulcerations during each scheduled visit. This will not be pursued at the interim visits when presenting with an acute upper respiratory disease as mucosal changes are likely to be present related to these syndromes. Subjects will be queried about any intraoral or systemic adverse reactions. Toxicity will be graded according to modification of the National Institutes of Health, National Institute of Allergy and Infectious Diseases, DMID Adult Toxicity Tables provided in Appendix 1.

Subjects will keep a daily diary of oral temperature, product usage adherence, typical cold and flu symptoms that may occur, school or work absenteeism, and visits to physicians’ offices, emergency departments and urgent care centers using REDCap electronic data capture tools hosted at University Hospitals Case Medical Center. REDCap (Research Electronic Data Capture) is a secure, web-based application designed to support data capture for research studies. Following the completion of the study, participants will be asked to take a short survey through the same REDCap system in order to assess the acceptability of the product and to gather information about the volunteers’ willingness to continue to use the product beyond the study parameters and if they would recommend the product to others. Finally, to further assess adherence to the study, product bottles will be counted.

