**Randomization and Withdrawal Procedures**

The randomization list will be generated and provided to the study pharmacist. The study blind (except for the Study Pharmacist) will be maintained by all study personnel. The investigators may request that the blind be broken for medical reasons.

Each subject will be encouraged to complete the full course of the intervention assignment and study assessments. However, it is understood that the subject may discontinue study participation at any time for any reason. In addition, subjects should be encouraged to return to the unit within 28 days after dropout for additional safety assessments. The reason for early withdrawal must be documented in the CRF and in the source documents. Subjects are free to withdraw from the study at any time for any reason. Subjects should normally be withdrawn from the trial if a serious adverse event (SAE) occurs. Exceptions must be discussed with the Sponsor.

Subjects **must** be withdrawn from the trial if:

1. They withdraw their consent;
2. The investigator considers it in the best interest of the subject that he or she is withdrawn;
3. They experience a grade 3 or 4 adverse event (AE) (Appendix 1)

The reason for any subject’s discontinuation and the date of withdrawal will be recorded in the subject’s CRF. The subject’s CRF, which will be completed up to the point of withdrawal. The study report will include reasons for subjects’ withdrawals as well as details relevant to the subjects’ withdrawals. Any subject withdrawn from the trial prior to completion will undergo all procedures indicated in this protocol as being scheduled to occur at discharge or upon early withdrawal, subject to his/her consent. Any subject withdrawn due to an adverse event (whether serious or non-serious) or any clinically significant abnormal laboratory test value will be evaluated by the Principal Investigator or a monitor (see Key Personnel), and will be treated and followed up until the symptoms or values return to normal or acceptable levels, as judged by the Principal Investigator.

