|  | Grade 1 | Grade 2 | Grade 3 | Grade 4 |
| Fever: oral | 37.7 - 38.5°C or  100.0 - 101.5°F | 38.6 - 39.5°C or  101.6 - 102.9°F | 39.6 - 40.5°C or  103 - 105°F | > 40°C or  > 105°F |
| Fatigue | normal activity reduced < 48 hours | normal activity decreased 25- 50% > 48 hours | normal activity decreased > 50% can’t work | unable to care for self |

| **ORAL** | | | | |
| --- | --- | --- | --- | --- |
| **Oral sites** | Grade 1 | Grade 2 | Grade 3 | Grade 4 |
| Mucosa  (buccal, labial, soft palate, and gingiva) (See Appendix 3 for more detail) | Erythema, and or superficial whitening and wrinkling of epithelium at contact site | Localized maculopapular lesions and or desquamation and ulceration | Diffuse vesiculation or desquamation and ulceration  (Lichenoid reaction) | Severe mucous membrane involvement or erythema, multiforme or suspected Stevens-Johnson or necrosis requiring surgery |
| Tongue | Erythema, altered papilla architecture or loss of papilla on dorsum of tongue | Localized desquamation, or ulceration localized | Diffuse vesiculation desquamation or ulceration  (Lichenoid reaction) | Severe mucous membrane involvement or erythema, multiforme or suspected Stevens-Johnson or necrosis requiring surgery |
| Floor of Mouth | Erythema, and or superficial whitening and wrinkling of epithelium at contact site | Localized desquamation or ulceration | Diffuse vesiculation or desquamation and ulceration  (Lichenoid reaction) | Severe mucous membrane involvement or erythema, multiforme or suspected Stevens-Johnson or necrosis requiring surgery |
| Palate | Erythema and or superficial whitening and wrinkling of epithelium at contact site | Localized maculopapular effects and or desquamation and ulceration | Diffuse vesiculization or desquamation and ulceration  (Lichenoid reaction) | Severe mucous membrane involvement or erythema, multiforme or suspected Stevens-Johnson or necrosis requiring surgery |
| Taste | Transient changes in taste perception  < 1 minute | Altered changes  Metallic, bitter last up to 1 hour | Lasting changes in taste >1 hour | Loss of taste |

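### Minor: in the oral fever row of Appendix 1, grades 3 and 4 overlap from 40.1 to 40.5°C, and 103.0–103.1°F is grade 3 in °F but grade 2 in °C

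*Protocol*

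**What the plan says.** The oral fever row stands in the Systemic part of the toxicity table in Appendix 1. Each grade has a Celsius limit and a Fahrenheit limit joined by the word or:

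- Grade 1: "37.7 - 38.5°C or 100.0 - 101.5°F"
- Grade 2: "38.6 - 39.5°C or 101.6 - 102.9°F"
- Grade 3: "39.6 - 40.5°C or 103 - 105°F"
- Grade 4: above 40°C or above 105°F

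The Study Outcome Measures section makes this the grading scale; toxicity follows a modification of the "DMID Adult Toxicity Tables provided in Appendix 1". Randomization and Withdrawal Procedures lists the conditions under which a subject must leave the trial. One is "They experience a grade 3 or 4 adverse event (AE) (Appendix 1"). Another leaves room for judgement: "The investigator considers it in the best interest of the subject that he or she is withdrawn".

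Temperature is collected daily. The diary instructions read "Subjects will also be asked to take their temperature at 5p.m. each day and record their temperatures in the diaries" and "Subjects will keep a daily diary of oral temperature, product usage adherence". Neither names a unit, and the fever row does not say which unit prevails.

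**The concern.** A grading row should give each reading one grade. This row fails in two ways.

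First, the Celsius limits overlap: grade 3 ends at 40.5°C, but grade 4 already begins above 40°C. Second, the Celsius and Fahrenheit limits are offered as equivalents but do not convert into one another, so the same temperature can get different grades depending on the unit used.

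The grade 2/3 line matters most, because grade 3 triggers mandatory withdrawal. Two subjects with nearly the same fever could be handled differently because one was graded in °F and the other in °C. Elsewhere in the row only the severity entered in the safety record is at stake.

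**Working it through.** **Inputs.** The four pairs of limits in the Appendix 1 row, and the rule that grades 3 and 4 both require withdrawal.

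**Formulas.** °F = 1.8 × °C + 32, and °C = (°F − 32) × 5/9. Readings are taken to 0.1 degree, and conversions are rounded to 0.1 before grading.

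**Step 1: do the printed pairs agree?**

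| Limit | Printed °C, converted to °F | Printed °F, converted to °C | Gap in °F |
|---|---|---|---|
| Grade 1 lower | 37.7 → 99.86 | 100.0 → 37.78 | 0.14 |
| Grade 1 upper | 38.5 → 101.30 | 101.5 → 38.61 | 0.20 |
| Grade 2 lower | 38.6 → 101.48 | 101.6 → 38.67 | 0.12 |
| Grade 2 upper | 39.5 → 103.10 | 102.9 → 39.39 | 0.20 |
| Grade 3 lower | 39.6 → 103.28 | 103 → 39.44 | 0.28 |
| Grade 3 upper | 40.5 → 104.90 | 105 → 40.56 | 0.10 |
| Grade 4 (above) | 40 → 104.00 | 105 → 40.56 | 1.00 |

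Six pairs agree to within 0.28°F. The grade 4 pair is a full 1.0°F apart.

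**Step 2: the overlap, within Celsius alone.** The readings 40.1, 40.2, 40.3, 40.4 and 40.5°C all lie in 39.6–40.5°C and all exceed 40°C, so each meets grades 3 and 4. The Fahrenheit column has no such overlap, since grade 3 ends at 105°F and grade 4 lies above it. The grade 3 upper limit (40.5°C), 105°F (40.56°C) and the Fahrenheit grade 4 limit agree to within 0.1°C. The 40°C limit is the odd one out.

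**Step 3: the grade 2/3 line.** (103.0 − 32) × 5/9 = 39.44°C, and (103.1 − 32) × 5/9 = 39.50°C. Both are grade 3 in °F (103–105) and grade 2 in °C (38.6–39.5). The next reading, 103.2°F, is 39.56°C; it rounds to 39.6°C and is grade 3 in both units. In Celsius the conflict is the single reading 39.5°C.

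**Step 4: the other mismatches.**

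- 37.7°C (99.86°F) is grade 1 in °C and ungraded in °F.
- 38.6°C (101.48°F) is grade 2 in °C and grade 1 in °F. The Fahrenheit readings concerned are 101.4 and 101.5°F (38.56 and 38.61°C).
- 105.0°F (40.56°C, rounds to 40.6°C) is grade 3 in °F and grade 4 in °C.

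**Step 5: which of these can change withdrawal?** Steps 2 and 4 cannot: each either stays below grade 3 in both units or lies at grade 3 or 4 in both. Only Step 3 crosses the withdrawal line.

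**The case against.** The strongest reply is that almost nothing turns on this. The overlap changes no action, because both grades require withdrawal. Appendix 1 also tells the clinician to treat any event judged serious or life-threatening as grade 4, which settles part of the overlapping band. Each unit taken alone runs without gap or overlap at the grade 1/2 and 2/3 lines, so those conflicts need readings graded in different units. The illness definition uses °C (above 37.8°C), which hints at a working unit. The investigator may withdraw a subject at any grade. And the row may have come unchanged from the named source scale.

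Most of this stands, and it keeps the point small, but it does not remove it. The clinician rule does not reach a fever of 40.1–40.5°C that is not judged serious. A Celsius threshold for illness does not fix the unit for the diary or for grading. Discretion to withdraw does not release anyone from mandatory withdrawal at grade 3. Whether the row was inherited cannot be seen from the protocol, so no drafting error by this sponsor is shown. Either way it is the text that investigators must apply, and the protocol already describes the table as a modification.

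A reader might infer more: that the overlap makes the withdrawal rule unworkable at high fever, or that the row threatens the efficacy result. The documents support neither. Withdrawal is the same on both sides of the overlap. The efficacy analysis compares the number and duration of illnesses, under a definition that does not use these grades.

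**Conclusion.** The row is wrong as written, at the lowest level of minor. Grade 4 above 40°C contradicts grade 3 up to 40.5°C, and the consequence is limited to recorded severity. The unit conflict at 103.0–103.1°F (39.5°C) is the only part that can change mandatory withdrawal, and only when the fever is recorded as an adverse event. The remaining mismatches affect the recorded grade alone.

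This assumes readings to 0.1 degree and ordinary rounding on conversion. The protocol gives no temperature distribution, so the number of subjects affected cannot be estimated. Randomization, the illness definition, the sample size and the efficacy comparison do not depend on the row.

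**What to change.** Change the grade 4 Celsius limit to above 40.5°C, and name one governing unit for the row and for the diary temperature. Then align the other unit. Either choice works:

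| Grade | °F governs (°C aligned) | °C governs (°F aligned) |
|---|---|---|
| 1 | 100.0–101.5°F (37.8–38.6°C) | 37.7–38.5°C (99.8–101.3°F) |
| 2 | 101.6–102.9°F (38.7–39.4°C) | 38.6–39.5°C (101.4–103.1°F) |
| 3 | 103.0–105.0°F (39.5–40.5°C) | 39.6–40.5°C (103.2–104.9°F) |
| 4 | >105.0°F (>40.5°C) | >40.5°C (>104.9°F) |

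**If °F governs,** every Fahrenheit limit stays as it is, and the Celsius withdrawal line tightens by 0.1°C, from 39.6 to 39.5°C. Grade each reading in the unit in which it was taken, or convert °C to °F. Do not convert °F to rounded °C: 103.0°F becomes 39.4°C and drops to grade 2, and 105.0°F becomes 40.6°C and rises to grade 4.

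**If °C governs,** the Fahrenheit limits are the readings that round to the Celsius ones: 99.8°F = 37.67°C, 101.4°F = 38.56°C, 103.2°F = 39.56°C and 105.0°F = 40.56°C. The Fahrenheit withdrawal line must be 103.2°F. A line at 103.3°F would create a new conflict, because 103.2°F rounds to 39.6°C, which is grade 3. The protocol should state the rounding rule and say that the Fahrenheit withdrawal line has moved up by 0.2°F.

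The cost is an edit to one table row, a footnote recording the change to the named scale, and the unit in the diary instruction. No extra data, visits or analyses are needed.

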**Appendix 2: Schedule of Events**

| **Procedure** | **Screening/Enrollment** | **Follow-up V1**  **(±7 days)** | **Follow-up V2**  **(±7 days)** | **Follow-up V3**  **(±7 days)** | **Final Study Visit**  **(within 2 months)** |
| --- | --- | --- | --- | --- | --- |
| Informed Consent | X |  |  |  |  |
| Medical History | X |  |  |  |  |
| Physical Exam | X |  |  |  |  |
| Serum Chemistries, CBC w/Diff, Serum Hcg | X |  |  |  |  |
| Review Inclusion/Exclusion | X |  |  |  |  |
| Interval Medical History | X |  |  |  |  |
| Posterior pharyngeal and Nasal Swab | X | X | X | X |  |
| Dispense Study Product | X | X | X |  |  |
| Study Diary Distributed | X | X | X |  |  |
| Review Study Procedures | X | X | X | X |  |
| Interval Medical & Concomitant Medication History |  | X | X | X | X |
| AE’s (solicited & unsolicited) |  | X | X | X | X |
| Review Study Diary |  | X | X | X |  |
| Oropharyngeal Exam |  | X | X | X | X |
| Symptom directed PE as indicated |  | X | X | X | X |
| Study Bottles collected counted |  | X | X | X |  |

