**Clinical/Laboratory Evaluations and Study Schedule**

**Screening/Enrollment (See Appendix 2, Schedule of Events)**

Written informed consent will be obtained before any clinical evaluations are performed. The study will consist of 2 groups randomly assigned to Halo or matching placebo. The study visits will be conducted in the CWRU School of Medicine Room 3080. Screening and Enrollment will be performed at the same visit, a complete medical history and physical exam will be performed by study clinicians along with, serum chemistries, CBC with differential count, and a serum pregnancy test for women. Randomization into the study will be undertaken when it is determined that the subject has met all study inclusion criteria and has no exclusion criteria other than possible lab results. Since the screening and enrollment will be conducted at the same visit, subjects will begin the study prior to results of labs. If the labs result in an exclusion criteria the subject will be notified to discontinue and return unused study product. As noted in the safety section:. the study product has an acceptable safety profile and poses no significant toxicological risk to individuals. The formulation consists of ingredients with a long history of safe use in oral healthcare products.

A posterior pharyngeal and nasal swab will be obtained to ascertain baseline bacterial and fungal organisms and a multiplex PCR for respiratory viruses. Study product (after randomization) will be provided until the next scheduled visit, study procedures will be again reviewed, contact information for reaching study personnel will be provided, and study diaries will be distributed. Appointments for the 1^st^ monthly evaluation will be made.

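### No oropharyngeal exam is named before first use, so the oral safety endpoint has no specified, graded baseline

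*Protocol*

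**What the plan says.** Protocol, Appendix 2 (Schedule of Events). The row "Oropharyngeal Exam" reads "Oropharyngeal Exam | | X | X | X | X": nothing at Screening/Enrollment, then V1, V2, V3 and the final visit. The enrolment column does carry "Physical Exam | X" and "Review Inclusion/Exclusion | X".

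Protocol, Screening/Enrollment. At this visit "a complete medical history and physical exam will be performed by study clinicians". No oropharyngeal exam and no Appendix 3 diagram is mentioned. The section also states that "Screening and Enrollment will be performed at the same visit", and product is handed out after randomization at that visit. Randomization follows once it is settled that the subject "has met all study inclusion criteria and has no exclusion criteria other than possible lab results".

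Protocol, Scheduled Follow-up Visits and Final Study Visit. Both name an oropharyngeal exam and an intra-oral exam recorded on the Appendix 3 diagram.

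Protocol, Study Outcome Measures. For safety and tolerance, "the oropharynx and gingiva will be examined for erythema and ulcerations during each scheduled visit".

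Protocol Schema. Examination inside and outside the mouth is the second listed endpoint, and tolerability belongs to the first secondary objective. In Appendix 1, grade 1 on the oral rows starts at erythema, superficial whitening or altered tongue papillae.

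**The concern.** The product is an antiseptic sprayed into the mouth, so mucosal change is the most direct local safety signal. The lowest oral grade consists of mild, non-specific signs that a healthy adult may show before any dose. If nobody records the mouth on the Appendix 1 scale before first use, such signs will first be recorded at V1, about a month into dosing, and may be read as effects of the product.

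Two things are at stake. Within a participant, a finding cannot be attributed. Across arms, the rates of oral findings are too high in both, and the contrast between them is weaker than it should be. A later analysis plan cannot repair this, because it cannot supply an exam that was not done.

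**Working it through.** The protocol states no figure on this point, so there is nothing to reproduce. The check is a comparison of sections, followed by an illustration of the direction of the effect.

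**Step 1: schedule against visit text.**

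| Visit | Appendix 2, oropharyngeal exam | Visit text |
| --- | --- | --- |
| Screening/Enrollment | blank | general history and physical exam only |
| V1, V2, V3 | marked | oropharyngeal exam and Appendix 3 diagram |
| Final visit | marked | oropharyngeal exam and Appendix 3 diagram |

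The exam is named at 0 of 1 enrolment visits and at 4 of 4 later scheduled visits. Table and text agree on the omission, so a broken table does not explain it. Appendix 2 lists the physical exam and the oropharyngeal exam as separate rows, so the first cannot be taken to include the second as specified.

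**Step 2: timing.** Screening, enrolment, randomization and dispensing fall on one visit. The first named oral exam is therefore at V1, on product.

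**Step 3: does Study Outcome Measures supply the baseline?** It promises the mucosal exam at each scheduled visit. There are two readings. If enrolment counts as a scheduled visit, the promise contradicts Appendix 2 and the enrolment text. If the term means the monthly visits after enrolment, which is how the same section uses it, no baseline is promised. Either way the text needs correcting.

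**Step 4: direction of the effect.** Let *b* be the prevalence of findings before dosing and *r* the true rate of new findings in an arm. Assume that baseline findings persist, are independent of new ones, and are all recorded as on-study. The apparent rate is then

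1 − (1 − *r*)(1 − *b*),

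and the apparent difference between arms is (1 − *b*) times the true difference. For any *b* above zero both rates rise and the difference shrinks towards zero. It does not move in favour of either arm.

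**Step 5: illustration.** The protocol gives neither *b* nor *r*; all values here are assumptions. With 51 per arm and new findings of 2% on placebo and 15% on Halo (true difference 13.0 points):

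| *b* | Pre-existing findings per arm (51 × *b*) | Apparent rates | Difference (points) | Exact power, Fisher test, two-sided 0.05 |
| --- | --- | --- | --- | --- |
| 0 | 0 | 2.0% vs 15.0% | 13.0 | 0.524 |
| 5% | 2.6 | 6.9% vs 19.3% | 12.4 | 0.338 |
| 10% | 5.1 | 11.8% vs 23.5% | 11.7 | 0.255 |
| 20% | 10.2 | 21.6% vs 32.0% | 10.4 | 0.166 |

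The loss depends heavily on the chosen pair. With 2% versus 30%, power goes from 0.98 at *b* = 0 to 0.91 at 5% and 0.81 at 10%. With 2% versus 8%, it is below 0.10 with or without a baseline. The protocol plans no Fisher test of oral findings, so these powers show direction only and do not measure the trial's actual loss.

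**The case against.** **The mouth may well be looked at.** A complete physical exam by a clinician can include the mouth, and the posterior pharyngeal swab taken at enrolment requires access to the throat. This stands in part: one cannot say that no baseline observation will exist. But nothing requires it to be recorded site by site or graded, and an ungraded glance cannot be compared with a graded V1 finding.

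**The oral-lesions exclusion.** A reader might infer that this exclusion is never checked and that the plan lets people with oral lesions be randomised. The protocol does not support that. Eligibility review and a physical exam are both scheduled at enrolment, and every non-laboratory exclusion must be settled before randomization. Enrolling someone with oral lesions would breach the protocol. What remains is that no named oral exam supports the check.

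**Baseline findings should be few.** Oral lesions, dentures and dental treatment in progress are excluded, so ulcerative findings should be largely absent. Grade 1 on the mucosa, floor-of-mouth and palate rows also refers partly to change where the product touches. This is fair, and it makes the upper end of the 5% to 20% range less plausible. Mild erythema or papilla change is not clearly excluded.

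**Randomization.** Pre-existing findings are balanced between arms in expectation. That stands: there is no bias in favour of either arm. The dilution and the loss of within-participant attribution remain.

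**Analysis convention.** How to tabulate new or worsened findings is commonly left to an analysis plan. That is so, but the exam it would depend on has to be in the visit schedule.

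**Conclusion.** The point holds as a gap in the schedule. Appendix 2 and the enrolment text name no oropharyngeal or diagram-based exam before first use, and the promise in Study Outcome Measures either contradicts them or does not reach enrolment. A listed safety endpoint therefore has no specified, graded pre-treatment baseline.

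The consequence is inflated apparent rates in both arms, a diluted contrast, and findings that cannot be classed as new, worsened or pre-existing. The direction follows for any non-zero baseline prevalence under the assumptions in Step 4. The size cannot be derived from the protocol. The primary efficacy comparison is unaffected. This is a cheap improvement that should be made, not a flaw that invalidates the trial.

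**What to change.** 1. In Appendix 2, mark the oropharyngeal exam under Screening/Enrollment.
2. In the Screening/Enrollment section, state that it is done before first use, recorded on the Appendix 3 diagram and graded on the Appendix 1 oral rows. Say in Study Outcome Measures that enrolment is among the scheduled visits meant there.
3. Summarise oral findings as new or worsened from baseline, in the protocol or the analysis plan.
4. Reconcile the text on interim illness visits. Study Outcome Measures says the mucosal safety exam is not done then, whereas the Interim Visits section calls for an oropharyngeal exam. The latter may be meant as diagnostic; if so, the protocol should say so.

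The cost is a few minutes of clinician time at a visit where the participant is already examined and swabbed, one mark in the table and a few sentences of text.
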